## Measurements

### Coding log

An NB coding log was designed to rate micro-level NBs of “smiling,” “gestures,” “eye contact,” and “positivity in tone of voice”, and macro-level NB impressions of “dominance, and being in charge” “overall positivity,” and “expressivity” in each NB video. Moreover, an item regarding “attractiveness” was added to the log as a rating for physical appearance of actors. The coders were asked to rate each NB based on their general impression on a scale from “1” anchored to “not at all,” to “9,” anchored to “extremely high.” The coding log was based on the “general impression” approach (Blanch-Hartigan et al., 2018). The log eventually included “eight” items. Each of the items, except attractiveness, was operationally defined for the coders (see Supplementary material, Section Definition of NBs, for the definitions).

### Short excerpts of NB videos

As the entire length of the videos for each NB condition was about 1 h, short excerpts or thin slices of the beginning, the middle, and the end (each about 1 min) of each phase (introduction, calibration, and so forth) and the conditions (the +FE, +TV, +BM, and the NC) were extracted and attached together, making a total duration of “3” min for each phase/condition (Blanch-Hartigan et al., 2018). Since the scenarios were played by two actors, each phase had two versions, each played by one actor, therefore making a total of 14 (7 phases played × 2 actors) excerpts.

### Procedure for coding

The coding was performed in groups, and all the excerpts were rated by all coders. The coders first watched the excerpt and then rated the NB rating scale on a shared Google document. The video and the audio were played at the same time for all excerpts, but for the +TV, the audio was played without the video. The coders were told to do the coding alone and without discussion with others. Furthermore, the coders were told not to change their responses once they finished the coding. Next, the coders coded all the excerpts in one session using the coding log. The item's attractiveness was coded once for each actor.

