### NB coders

Fifteen Norwegian (11 females, 4 males; Mean age = 22.8; *SD* = 1.28) and six US (5 females, 1 male; Mean age = 21.3; *SD* = 1.54) undergraduate psychology students performed the coding. The Norwegian students performed the coding as part of their course “Bachelor Thesis in Psychology” at NTNU, in the spring semester of 2021. The US students were research assistants working in the second author's laboratory for course credit in the spring semester of 2021. The coders received training on how to use the coding log and perform the coding. The NB coding task can be done with a minimum of two coders (van Osch et al., 2017; Blanch-Hartigan et al., 2018); however, in this study, 21 coders from two different cultures were recruited.

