### Statistical analyses and data screening

IBM SPSS Statistics 27.0 and STATISTICA version 7 were used. To test the reliability of the NB ratings, first, the inter-rater reliability between coders was assessed using eight intra-class coefficients (Cicchetti, 1994), and, next, internal consistency was assessed using Cronbach's alpha, separately for the Norwegian and US data, with each including eight internal consistency analyses. Next, the internal consistency and intra-class coefficients of NB ratings were tested across the three actors. The potential differences in NB ratings between actors and countries were also tested. Due to the low number of coders in the US group and the unequal *N* of the groups, two Kruskal–Wallis (K–W) non-parametric tests were separately run: the first one to test the differences in the NB ratings between countries and the second to test the differences in the NB ratings between actors.

To test the amplitude of NBs in each condition, seven one-way repeated measures ANOVA were conducted on the overall data from both the Norwegian and the US samples, as the ratings from both groups were similar. However, as there were no significant differences between the introduction, calibration, and pre-test, only the positively enhanced conditions of the +FE, +TV, +BM, and NC were tested. For these analyses, the design was with four NB conditions (+FE, +TV, +BM, and NC) as the factor on the NB ratings (i.e., dependent variables) of smile, eye contact, positivity in tone of voice, and gestures. A one-way repeated measures ANOVA was run for each NB-dependent variable.

To test the effects of micro-level NBs on impressions of dominance, overall positivity, and expressivity, repeated measures with four NBs (+FE, +TV, +BM, and NC) were used. Three one-way repeated measures ANOVAs with NBs as the factors, one for each NB impression, were performed. All significant main effects were followed up using the *Tukey* HSD.

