### Construct validity of the manipulated NB conditions

There were no differences in the rating of NBs between the introduction, calibration, and pre-test (see Supplementary Table on page 21). Therefore, these phases are not analyzed further.

As expected, the +BM had higher gestures than the other conditions [*F*_(3, 18)_ = 225.74, η^2^ = 0.97]. The +FE had higher eye contact [*F*_(3, 18)_ = 97.29, η^2^ = 0.94] and smiles [*F*_(3, 18)_ = 127.96, η^2^ = 0.95] than the other conditions. The +TV had higher positivity in tone of voice than the other conditions [*F*_(3, 18)_ = 64.56, η^2^ = 0.91]. The +BM and +TV had higher smiles than the NC (*P*s < 0.001), and the +FE and +BM had higher positivity in tone of voice than the NC (*P*s < 0.001). The +FE was more positive in tone of voice compared to the +BM (*P* = 0.003), and the +BM had higher eye contact compared to the +TV (*P* = 0.049) (Figure 3).

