There were differences in the rating of physical attractiveness between actors, and physical attractiveness can affect social interactions (Reis et al., 1980, 1982) and placebo effects (e.g., Yan et al., 2018). The main aim of this experiment is to test the effects of the NBs of caregivers on the amplitude of pain reports and placebo effects. Therefore, to control for the effects of attractiveness, two actors with the higher and lower ratings of physical attractiveness will be used in each NB group of the +FE, +TV, +BM, and the NC. Thus, participants in each group will either see the actor with a higher rating or lower rating of attractiveness, and the sum of the two sub-groups will be used in the analyses. This approach may control for the confounding effects of attractiveness.

The NBs were expressed as intended. That is, the +FE had more smiling and eye contact, the +TV had higher positivity in tone of voice, and the +BM had more positive body movements and gestures compared to the NC and other conditions. The introduction, calibration, and pre-test were like the NC, having the lowest rates of NBs. This indicates that the NBs were as they were intended to be. So, in neutral conditions (introduction, calibration, pre-test, and the NC), the NBs were low as intended, and in positive conditions (+FE, +TV, and +BM), the NB(s) that were at the focus had the highest level, confirming the validity of the NB conditions. However, in positive NBs, NBs other than the NB of the focus increased as well. For example, in +BM, which had the highest gestures, eye contact was also increased. This can be due to the quality of the NBs, as some NBs can affect the other NBs (Dittmann, 1972); for example, tone of voice is affected when a welcoming body posture or a leaning forward is expressed (Dittmann and Llewellyn, 1969). Similarly, an increase in smiling was observed in the +TV, which can be partly explained by the physiological structure of the muscles involved in the production of certain NBs, such as the tone of voice and its effects on facial expressions (e.g., Campanella and Belin, 2007). However, the NBs of the focus were still the highest among the other NBs, confirming the validity of the NB manipulations.

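### As described, coders heard the +TV excerpts without picture, so the preparatory study does not show that the +TV film is visually neutral, and its +TV contrasts mix condition with presentation mode

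*Protocol article*

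**What the plan says.** All places are in the protocol article.

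- **Procedure for coding:** picture and sound ran together for the excerpts, "but for the +TV, the audio was played without the video". The same section states that "all the excerpts were rated by all coders".
- **Coding log:** "An NB coding log was designed to rate micro-level NBs of “smiling,” “gestures,” “eye contact,” and “positivity in tone of voice", plus three overall impressions (dominance, positivity, expressivity) and attractiveness.
- **Statistical analyses and data screening:** for the micro-level items, "the design was with four NB conditions (+FE, +TV, +BM, and NC) as the factor on the NB ratings". The three impressions were analysed over the same four conditions.
- **Construct validity of the manipulated NB conditions:** two results on visual items involve +TV. "The +BM and +TV had higher smiles than the NC" (P < 0.001), and "the +BM had higher eye contact compared to the +TV" (P = 0.049).
- **Discussion:** "an increase in smiling was observed in the +TV". The text explains this by the muscles that produce the voice, and concludes that the conditions are valid.
- **NB scenarios and Procedure:** in +TV, everything except the voice was to be as neutral as possible. The videotaped experimenters appear on a 70-inch screen in front of the participant.

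**The concern.** Smiling, eye contact and gestures cannot be seen in a sound recording. If +TV was played as described, its scores on these three items are at best inferences from the voice. They cannot show whether the face, gaze and body in the +TV film were neutral, yet that film, with its picture, is what the trial will use.

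The items that can be judged from sound are affected differently. For tone of voice, dominance, positivity and expressivity, +TV was heard only, while +FE, +BM and NC were seen and heard. A difference between +TV and any of them may come from the condition, from the missing picture, or from both.

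At stake is how the trial will be read. The second general aim ranks +FE above the other groups. The Introduction criticises earlier work because several behaviours varied together and no single one could be credited. If the +TV film does carry more smiling than NC, +TV v NC and +FE v +TV cannot be read as effects of single channels.

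**Working it through.** **1. Were +TV ratings of the visual items really in the analyses?** Inputs: 21 coders (NB coders: "in this study, 21 coders from two different cultures were recruited", made up of 15 Norwegian and 6 US); k = 4 conditions; F(3, 18) printed for gestures, eye contact, smiles and tone of voice.

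The multivariate repeated-measures test has degrees of freedom (k − 1, N − k + 1).
- With +TV, k = 4: (3, 21 − 4 + 1) = (3, 18), as printed.
- Without +TV, k = 3: (2, 21 − 3 + 1) = (2, 19), which is not what is printed.

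Partial η² = df1·F / (df1·F + df2) supports the same reading:

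| Item | F | Calculation | Result | Printed |
|---|---|---|---|---|
| Gestures | 225.74 | 677.22 / 695.22 | 0.974 | 0.97 |
| Eye contact | 97.29 | 291.87 / 309.87 | 0.942 | 0.94 |
| Smiles | 127.96 | 383.88 / 401.88 | 0.955 | 0.95 |
| Tone of voice | 64.56 | 193.68 / 211.68 | 0.915 | 0.91 |

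The printed values agree, with smiles cut off rather than rounded. For the impression ANOVAs, whose degrees of freedom are fractional, df2/df1 + 1 gives the number of coders:
- dominance: 40.56/2.02 + 1 = 21.1
- positivity: 51.09/2.55 + 1 = 21.0
- expressivity: 58.34/2.91 + 1 = 21.0

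So all 21 coders contributed +TV ratings to the visual-item ANOVAs, and the impression ANOVAs imply the same number. This check shows that the ratings were analysed. It does not show whether they were made from sound alone; that rests on the coding procedure.

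**2. What could each rating rest on, taking the coding procedure as written?**

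| Item | +TV | +FE, +BM, NC |
|---|---|---|
| Smile, eye contact, gestures | nothing visible | picture and sound |
| Tone of voice | sound | picture and sound |
| Dominance, positivity, expressivity | sound | picture and sound |

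Three of the four micro-level items have no visible stimulus behind the +TV score. The other micro-level item and the three impressions compare different modes. Together these are the 4 + 3 = 7 ANOVAs. Comparisons among +FE, +BM and NC share one mode and are not affected.

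**3. Does another part of the article fill the gap?** No coding of the +TV picture is reported. The separate study mentioned in the Discussion tested incongruency between behaviours, with preliminary results, and is not described as a test of visual neutrality. The supplement is not at hand.

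**The case against.** **The coders may have seen +TV.** The Coding log section speaks of rating each video, Procedure for coding says coders watched each excerpt before rating, and the Discussion gives a facial-muscle explanation for +TV smiling. The audio-only clause might loosely describe how the voice item was rated. This stands as a possibility, and the fix allows for it. But the clause makes no such restriction, and +TV names the condition throughout. On that reading the clause itself needs correcting.

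**Spill-over is already disclosed.** The Discussion and Expected limitations say that behaviours other than the target also rose, and that channels were enhanced rather than separated. This is fair: the article does not claim pure isolation. It does not cure the point, because for +TV the disclosure rests on the same ratings made without a picture.

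**The trial itself is untouched.** Randomisation, pain outcomes and the comparison between assigned videos do not depend on the coding study. This stands, and it limits the point to interpretation.

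**Stronger readings that a reader might infer.**
- That +TV was never visually validated anywhere: the documents support only that the preparatory study, as described, does not do so.
- That the absence of a dominance effect for +TV is an artefact of the missing picture: this is possible but not shown. +TV was still rated above NC on positivity and expressivity, so a missing picture did not lower every impression below NC, and no direction of bias is established.
- That the +TV arm's trial results would be biased: no bias in any trial estimate is demonstrated. The 20 of 80 participants are the size of the arm, not of an error.

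**Conclusion.** The point holds in limited form. Taking the coding procedure as written, the visual ratings for +TV have no visual basis, and the validity conclusion in the Discussion goes too far for that condition. Three of seven ANOVAs include +TV scores on items that could not be seen; the other four include +TV contrasts confounded with presentation mode. The size and direction of any distortion cannot be derived from the article.

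The randomised contrasts between assigned videos remain sound. Crediting a +TV effect, or a +FE v +TV difference, to tone of voice alone is not supported until the visual content of the +TV film is known. The conclusion assumes that the audio-only statement is accurate and that the supplement, which is not shown, contains no separate coding of the +TV picture.

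**What to change.** State plainly how the +TV excerpts were presented for each item.

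- **If audio only:** remove +TV from the smile, eye-contact and gesture ANOVAs. Flag its contrasts on tone, dominance, positivity and expressivity as confounded with presentation mode. Delete the statement that smiling was observed in +TV. Limit the validity conclusion in the Discussion to say that +TV's visual neutrality is not established.
- **If coders did see the +TV picture for the visual items:** correct Procedure for coding to say so, and say which items were rated from sound alone.

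The minimum cost is a re-run of three ANOVAs and some wording, with a weaker validity claim for +TV.

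Re-rating is optional. It should present all four conditions in the same mode and session, because re-rating +TV alone would swap a mode difference for a session difference. At 3 minutes per excerpt this means 4 × 2 × 3 = 24 minutes of viewing per coder with two actors (Short excerpts of NB videos), or 4 × 3 × 3 = 36 minutes with three (Videotaped experimenters). Whether the 2021 student coders are still available is not known.

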### Statistical analyses and data screening

IBM SPSS Statistics 27.0 and STATISTICA version 7 were used. To test the reliability of the NB ratings, first, the inter-rater reliability between coders was assessed using eight intra-class coefficients (Cicchetti, 1994), and, next, internal consistency was assessed using Cronbach's alpha, separately for the Norwegian and US data, with each including eight internal consistency analyses. Next, the internal consistency and intra-class coefficients of NB ratings were tested across the three actors. The potential differences in NB ratings between actors and countries were also tested. Due to the low number of coders in the US group and the unequal *N* of the groups, two Kruskal–Wallis (K–W) non-parametric tests were separately run: the first one to test the differences in the NB ratings between countries and the second to test the differences in the NB ratings between actors.

To test the amplitude of NBs in each condition, seven one-way repeated measures ANOVA were conducted on the overall data from both the Norwegian and the US samples, as the ratings from both groups were similar. However, as there were no significant differences between the introduction, calibration, and pre-test, only the positively enhanced conditions of the +FE, +TV, +BM, and NC were tested. For these analyses, the design was with four NB conditions (+FE, +TV, +BM, and NC) as the factor on the NB ratings (i.e., dependent variables) of smile, eye contact, positivity in tone of voice, and gestures. A one-way repeated measures ANOVA was run for each NB-dependent variable.

To test the effects of micro-level NBs on impressions of dominance, overall positivity, and expressivity, repeated measures with four NBs (+FE, +TV, +BM, and NC) were used. Three one-way repeated measures ANOVAs with NBs as the factors, one for each NB impression, were performed. All significant main effects were followed up using the *Tukey* HSD.

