### Videotaped experimenters

Three Norwegian female professional actors in the age range of 26–32 played VEs. The actors were typecast to fit a usual health personnel stereotype (Mercer et al., 2008), wearing a white lab coat and light makeup. All NB conditions were played by all three actors (Figure 1). Before recording, each actor received about 10 h of training with the playscripts. VEs have been used in previous studies (Hunter et al., 2014; Ruben et al., 2017). To ascertain the validity of NBs, all video conditions were played by all actors.

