### Differences in NB ratings between actors

The second K–W test showed that the actors were rated similarly in gestures, eye contact, smile, tone of voice, dominance, expressivity, and overall positivity (*P* > 0.058); however, actor 1 had more gestures [*H*(2) = 10.92, *P* = 0.004] and eye contact [*H*(2) = 7.28, *P* = 0.02] than the other two; and actor 3 smiled more [*H*(2) = 16.34, *P* = 0.001]. Actors were rated differently regarding the attractiveness [*H*(2) = 19.40, *P* = 0.001].

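### The preparatory study compares actors with an independent-samples test although every coder rated every excerpt, so its non-significant items do not establish that the actors are similar.

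*Protocol article*

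**What the plan says.** The section Statistical analyses and data screening states that "two Kruskal–Wallis (K–W) non-parametric tests were separately run", one for countries and "the second to test the differences in the NB ratings between actors". The reason given for the choice is "Due to the low number of coders in the US group and the unequal *N* of the groups".

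Under Procedure for coding, "all the excerpts were rated by all coders". Under NB coders, "in this study, 21 coders from two different cultures were recruited" (15 Norwegian, 6 US).

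Under Differences in NB ratings between actors, the article reports that "the actors were rated similarly in gestures, eye contact, smile, tone of voice, dominance, expressivity, and overall positivity" with P > 0.058. The same sentence then reports that actor 1 had more gestures (H(2) = 10.92, P = 0.004) and eye contact (H(2) = 7.28, P = 0.02), and that actor 3 smiled more (H(2) = 16.34, P = 0.001). Attractiveness also differed (H(2) = 19.40, P = 0.001). The Discussion concludes that the results overall support similarity between actors, while conceding individual differences in amplitude.

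On the material coded, Videotaped experimenters says "All NB conditions were played by all three actors", whereas Short excerpts of NB videos says "Since the scenarios were played by two actors, each phase had two versions", giving 7 × 2 = 14 excerpts.

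**The concern.** Kruskal–Wallis treats the ratings of the three actors as coming from three separate sets of raters. Here the same 21 coders supply all of them. Stable differences between coders then sit in the error term, where a test blocked on coder would remove them. The stated reason, a small and unequal US group, concerns the country comparison and has no bearing on a contrast made within every coder. The article itself treats coder as a block when it compares NB conditions by repeated-measures ANOVA.

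A non-significant result from a mismatched test is then read as evidence of similarity. At stake is what the article may say about the videos: whether the actors deliver each non-verbal behaviour at comparable strength, and which actor-by-condition videos were validated.

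**Working it through.** **1. The reported figures.** The upper tail of chi-square on 2 df is exp(−H/2):

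| Item | H | P recomputed | P stated |
|---|---|---|---|
| Gestures | 10.92 | 0.0043 | 0.004 |
| Eye contact | 7.28 | 0.026 | 0.02 |
| Smile | 16.34 | 0.0003 | 0.001 |
| Attractiveness | 19.40 | 0.00006 | 0.001 |

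The gestures figure reproduces, and the others lead to the same conclusions as stated. This is consistent with three actor groups compared by the named test.

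**2. Effect of ignoring the pairing.** Let ρ be the within-coder correlation and take one value per coder and actor. The variance of a difference between two actor means is proportional to 2(1 − ρ), but the test scales it as if it were 2. In large samples H therefore behaves as (1 − ρ) times a chi-square on 2 df, and the true type I error is about 0.05^(1/(1−ρ)). At ρ = 0.3 this is 0.05^1.43 = 0.014; at ρ = 0.5 it is 0.05² = 0.0025.

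The article does not give ρ, so a range is assumed. Simulation of 21 coders × 3 actors (20,000 data sets per setting, normal coder effect with variance ρ, residual variance 1 − ρ) gave:

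| ρ (assumed) | Type I error, Kruskal–Wallis | Power, Kruskal–Wallis | Power, Friedman | Power, repeated-measures F |
|---|---|---|---|---|
| 0 | 0.045 | 0.33 | 0.27 | 0.35 |
| 0.1 | 0.037 | 0.31 | 0.29 | 0.38 |
| 0.3 | 0.016 | 0.28 | 0.36 | 0.47 |
| 0.5 | 0.004 | 0.24 | 0.49 | 0.62 |
| 0.7 | 0.001 | 0.19 | 0.71 | 0.85 |

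Power is for one actor shifted by 0.5 SD. The Friedman test held about 0.05 throughout. Rounding the ratings to a 1–9 scale changed little (type I error 0.018 at ρ = 0.3, 0.004 at ρ = 0.5).

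**3. The borderline P.** Take the smallest non-significant P as about 0.058. Then H = −2 ln(0.058) = 5.69, against a cutoff of −2 ln(0.05) = 5.99. Since 1 − 5.69/5.99 = 0.05, the large-sample rescaling would carry that item past the cutoff once ρ exceeds about 0.05.

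**4. Is a positive ρ plausible?** The country mean ranks allow H to be rebuilt. For smile, 12/(21 × 22) × [15(8.67 − 11)² + 6(16.83 − 11)²] = 7.41; for dominance the same formula gives 6.01. Dividing by 20 gives 0.37 and 0.30, so country accounts for about 30–37% of the rank variance between coders on the five items reported. Coders thus differ systematically in level, which makes a positive ρ likely but does not estimate it.

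**5. Can the direction reverse?** The article does not say whether the actor test used one value per coder and actor. With four ratings per cell entered as independent (coder variance 0.3, residual variance 0.7) and a coder-by-actor variance of 0.3 to 0.5, simulated type I error was 0.13 to 0.19 with no spread between conditions. With a large spread (condition means 0, 2, 2, 3) it was 0.016 to 0.049. Without any coder-by-actor variance it was 0.016 or lower.

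**6. Items listed twice.** Gestures, eye contact and smile appear in the list of items rated similarly and again as significantly different. That leaves four items reported only as non-significant: tone of voice, dominance, expressivity and overall positivity.

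**7. The excerpts.** Three actors in four NB conditions make 4 × 3 = 12 condition videos. Two versions of each make 4 × 2 = 8. The actor test nevertheless has three groups. If each phase was coded for only two of three actors, actor is partly mixed with condition, and condition effects are very large (gestures F = 225.74, η² = 0.97). The article does not say which actors were coded in which condition.

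**The case against.** Several points on the other side are sound.

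- A reader might infer that the test missed actor differences in general. It did not: it found differences in gestures, eye contact, smile and attractiveness. Only the four remaining items could hide one, and nothing in the article shows that they do.
- A reader might take over-conservatism as established. It needs a positive within-coder correlation and one value per coder and actor, and the article states neither. At ρ of 0 to 0.1 the Friedman test has no power advantage, and step 5 shows that the error can go the other way.
- A reader might suppose that the trial pools actors because they were found similar. The Discussion gives a different reason: the actors differ in attractiveness, so a higher- and a lower-rated actor are used in every group.
- A reader might fear confounding between arms. The Figure 2 legend says each group has two second experimenters, with participants randomly assigned to one of them. Both actors therefore appear in every arm.
- A country term might seem necessary. With coder as block and every coder rating every excerpt, a country main effect leaves the actor contrast unchanged.

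It can also be said that similarity has other support, namely alpha and ICC of at least 0.72 in Inter-rater reliability between actors. This does not rescue the claim. Alpha is unaffected by constant shifts in mean level, so it cannot show equal amplitude between actors, and the article does not say whether the ICC measures consistency or absolute agreement.

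Finally, this is a secondary check in a completed preparatory study, and no planned test or sample size depends on it. That limits the weight of the point but not its correctness.

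**Conclusion.** The point holds in limited form. The actor test does not match the crossed rating design, and the reason given for it does not apply to actors. The test is probably conservative, with type I error about 0.016 at an assumed within-coder correlation of 0.3 and 0.004 at 0.5, given one value per coder and actor. The true correlation and the data layout are not stated, so neither the size nor the direction is certain.

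Two conclusions need no assumption. Non-significance at P > 0.058 does not establish similarity, and the results sentence contradicts itself on gestures, eye contact and smile. The two-actor and three-actor descriptions also need reconciling. The documents do not support the further inference that undetected actor differences exist or that the randomised comparison is biased.

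**What to change.** - Re-analyse the existing ratings with a mixed model: actor and condition as fixed effects, coder as random block. If several ratings per coder and actor are used, add a coder-by-actor random term. Use the Friedman test only if the actor layout is complete, since it would not separate actor from condition otherwise.
- Report actor differences with confidence intervals for all seven behaviour and impression items.
- Remove gestures, eye contact and smile from the list of items rated similarly unless the new results support them. Restrict the similarity wording for the other items, and the matching conclusion in the Discussion, in the same way.
- List which actor-by-condition excerpts were coded, and reconcile the two-actor, 14-excerpt description with the three actors named and compared elsewhere.

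The cost is a short re-analysis of data already in hand and some rewording. The downside is that the actor-similarity statement may weaken. The trial design does not have to change.

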### Inter-rater reliability of NB rating

Table 1 Inter-rater reliability tests using Cronbach's α and intra-class coefficients (Cicchetti, 1994) showed high internal consistency in NB coding between coders both in the Norwegian and the US groups.

**Table 1 T1:** Cronbach's α and intra-class coefficients between the coders across coding groups and items.

**Coding items**	**Norwegian α**	**The US α**	**Norwegian ICC**	**The US ICC**
Gesture	0.99	0.98	0.99	0.98
Smile	0.99	0.92	0.99	0.96
Eye contact	0.99	0.86	0.99	0.92
Positivity in tone of voice	0.97	0.86	0.96	0.86
Dominance	0.83	0.85	0.82	0.66
Overall positivity	0.98	0.91	0.97	0.85
Expressiveness	0.98	0.93	0.96	0.91

ICC, intra-class coefficients using two-way mixed effects model. Cronbach's α: values ≥ 0.70 = acceptable reliability. ICC: values ≥ 0.60 = acceptable reliability. N of Norwegian coders: 15; N of the US coders: 6.

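### The preparatory study compares actors with an independent-groups test although the same coders rated every excerpt, so actor similarity in tone of voice, dominance, expressivity and overall positivity is not supported

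*Protocol article*

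**What the plan says.** The section Statistical analyses and data screening states that "two Kruskal–Wallis (K–W) non-parametric tests were separately run": one compares countries, and "the second to test the differences in the NB ratings between actors". The reason given for the choice is "Due to the low number of coders in the US group and the unequal *N* of the groups". For the four conditions, rated by the same people, that section uses repeated-measures ANOVA instead.

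On the design, Procedure for coding says that "all the excerpts were rated by all coders", and NB coders says that "in this study, 21 coders from two different cultures were recruited" (Table 1: "N of Norwegian coders: 15; N of the US coders: 6").

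On the result, Differences in NB ratings between actors reports that "the actors were rated similarly in gestures, eye contact, smile, tone of voice, dominance, expressivity, and overall positivity", with P above 0.058. The same sentence goes on to report that actor 1 was higher on gestures and eye contact and actor 3 on smiling. The Discussion then treats the results overall as supporting similarity between actors, while acknowledging individual differences.

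**The concern.** Kruskal–Wallis assumes that the groups being compared are independent sets of observations. That is right for country, where the coders are different people. It is not right for actor, where each coder appears in every group. The stated reason, few US coders and unequal group sizes, has no bearing on actors: every actor was judged by the same panel.

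At stake is the part of the preparatory study's second hypothesis that says ratings are similar across actors. That claim supports combining participants who see different actors within one behaviour group. For tone of voice, dominance, expressivity and overall positivity it rests on a non-significant result from a test that does not fit the data. Tone of voice is itself one of the trial's manipulations.

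**Working it through.** **Inputs from the article.** 15 + 6 = 21 coders; three actors (df = 2); all coders rate all excerpts; actor results H(2) = 10.92 (gestures), 7.28 (eye contact), 16.34 (smile), 19.40 (attractiveness).

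**Assumed.** Nominal level 0.05; correlation rho between one coder's scores for different actors, taken over a range because it is not reported.

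**1. Reproduce the reported test.** With 2 df the chi-square tail is P = exp(−H/2).
- Gestures: exp(−5.46) = 0.0043 (stated 0.004).
- Eye contact: exp(−3.64) = 0.026 (stated 0.02).
- Smile: exp(−8.17) = 0.0003 (stated 0.001).
- Attractiveness: exp(−9.70) = 0.00006 (stated 0.001).

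The gestures figure reproduces. The values fit a Kruskal–Wallis test on three groups with no blocking on coder.

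**2. What was one observation?** For the country test on smile, the rank total is 15 × 8.67 + 6 × 16.83 = 231.03, and 21 × 22/2 = 231. So that test used one value per coder. On the same basis the actor test has 21 × 3 = 63 values, dependent in sets of three. The article does not say whether the actor test was built this way.

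**3. Size if one score per coder and actor was used.** Kruskal–Wallis scales actor differences by the total spread of ranks, which includes spread between coders. Actor differences within a coder vary only by the share 1 − rho. Under no difference, H therefore behaves roughly as (1 − rho) times a chi-square on 2 df, and the size is about 0.05^(1/(1 − rho)). At rho 0.2 this is 0.05^1.25 = 0.024. Simulation of 21 coders by 3 actors is more reliable at higher rho:

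| rho | true size at nominal 5% |
|---|---|
| 0.2 | 2.4% |
| 0.4 | 0.8% |
| 0.6 | 0.2% |

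In companion runs of the same layout (rho 0 to 0.7), Friedman's test held 5.0% to 5.3%.

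**4. Power when one actor differs by 0.5 SD.**

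| rho | Kruskal–Wallis | Friedman |
|---|---|---|
| 0 | 0.33 | 0.27 |
| 0.2 | 0.30 | 0.33 |
| 0.3 | 0.28 | 0.36 |
| 0.5 | 0.24 | 0.49 |
| 0.7 | 0.19 | 0.71 |

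Scores rounded to the 1–9 scale gave the same pattern. Friedman gains only once rho is appreciable; with three actors it is inefficient at low rho.

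**5. How fragile is a P near 0.058?** If 0.058 is an observed minimum (not stated), H = −2 ln 0.058 = 5.69. For a repeated-measures or mixed model, H/(1 − rho) is a rough guide: at rho 0.2, 5.69/0.8 = 7.12 and exp(−3.56) = 0.028. This does not carry over to Friedman. Given H near 5.69, its median P was about 0.055 at rho 0.2 and fell below 0.05 only near rho 0.3.

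**6. If excerpt-level ratings were pooled.** With rho 0.3, four excerpts per actor and excerpt-to-excerpt SD 0.3, the type I error of Kruskal–Wallis was 0.07 to 0.29. Without excerpt variation it was below 0.001. The direction of the error therefore depends on the data layout.

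**The case against.** The strongest reply has four parts.

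- **The test did find differences.** It rejected on gestures, eye contact, smile and attractiveness. A reader might infer that the analysis made the actors look alike throughout, or hid a difference in smiling. The article does not support that, since those differences are printed. This stands, and it narrows the point to four items.
- **Direction and size are not established.** The correlation is not reported, and the unit of analysis in the actor test is not stated. US mean ranks of 16–17 against about 9 on five items make a positive correlation plausible, but ranks do not give the share of rating variance due to coder. This stands: conservatism is conditional, and the sizes are a range.
- **The similarity claim has other support.** Between-actor reliability coefficients were at least 0.72, and the Discussion concedes individual differences. This helps only in part: consistency among ratings does not show that actors have equal levels.
- **The consequence for the trial is small.** A reader might infer that actor differences confound the comparison of behaviour groups. The article does not support this. Each group uses two second-phase actors, chosen as higher and lower in rated attractiveness, with participants randomly assigned to one, so an actor main effect is spread across groups. This stands. What remains is a difference between actors in how strongly they deliver a given condition.

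None of this makes an independent-groups test valid for ratings by the same coders.

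**Conclusion.** The mismatch follows from the text alone: actor is a within-coder factor and was tested as if between coders. The test is invalid for that comparison whichever way the data were arranged. It is conservative, with the sizes tabulated above, only under one score per coder and actor and positive correlation.

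The claim of similar ratings fails in two ways. For gestures, eye contact and smile, its own sentence contradicts it. For tone of voice, dominance, expressivity and overall positivity, it rests on non-significance from the wrong test, and even a valid non-significant test would not show similarity. It would go too far to say that these four items do differ between actors, or that a correct analysis would turn P = 0.058 into a significant result: the first cannot be known without the ratings, and the second depends on rho and on the method chosen.

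This is worth correcting because it bears on the validation of the manipulation, but it does not undermine the randomised comparison of groups.

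**What to change.** Replace the second Kruskal–Wallis test by a mixed model on the existing ratings, with coder as random effect and actor, condition and actor by condition as fixed effects. The country test can stay as an independent-groups comparison.

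The mixed model is preferable to Friedman for two reasons: Friedman is inefficient with three actors, and the balance is unclear. Videotaped experimenters and the analysis section speak of three actors, whereas Short excerpts of NB videos describes two per phase and 7 × 2 = 14 excerpts. Reconcile these and state which actor was rated in which phase. If some actor–condition cells are empty, the interaction can be estimated only where cells are filled.

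Report actor and actor-by-condition differences with confidence intervals, and rewrite the similarity statements in Differences in NB ratings between actors and in the Discussion from those intervals.

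Cost: a re-analysis of ratings already in hand, with no new data. The downside is that more actor differences may have to be reported.
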